### Participants and recruitment

For the longitudinal part and process evaluation of our study we will recruit participants. The cross-sectional part of the study only includes generally collected data whereby recruitment of participants is not applicable. For the longitudinal part of our study, children in the so called groups 5 to 8 are enrolled in the study, which is internationally comparable with children in the 3rd to 6th grade. In these ‘groups’ children have the age to be able to validly complete self-report questionnaires. In the Dutch educational system, children attend primary school from the age of 4 until the age of 11 or 12, where they proceed to secondary school.

During the intervention period, the children of the participating schools (approximately *N* = 475) are asked to complete the questionnaires during five assessment points. Therefore, the population will consist of a dynamic cohort throughout the school years (Table 1). Parents are informed about the study with a school letter and an announcement in the school newsletter. Also, the researcher will be present at the school or during parent meetings to inform them about the study. In case parents don’t want their child to participate in the research study, they can inform the school or the researcher (opting-out procedure). The child’s questionnaires will be administered during the regular classes where a member of the research team is available to ensure independent and confidential responding and to provide assistance when necessary.

**Table 1 Tab1:** Overview longitudinal cohort assessments

Cohort	T1 (Sep-Nov 2016)	T2 (May-Jun 2017)	T3 (Sep-Nov 2016)	T4 (May-Jun 2018)	T5 (Sep-Nov 2018)
A					Group 5
B			Group 5	Group 5	Group 6
C	Group 5	Group 5	Group 6	Group 6	Group 7
D	Group 6	Group 6	Group 7	Group 7	Group 8
E	Group 7	Group 7	Group 8	Group 8	
F	Group 8	Group 8			

The population of the process evaluation includes participants on school-level and family-level. All educational staff working at the four primary schools are invited to participate anonymously by completing a questionnaire five times during the study period. These time points are similar to the assessments of the children and will be administered on paper or using an online survey platform. Also, the schoolboard, parents, and policy and practice stakeholders of the municipality of Amsterdam will be included as a participant in this process evaluation.

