### Statistical analyses

#### Power calculation for the primary outcome

At the start of our study the four schools have respectively 82, 119, 121, and 155 children in the targeted groups (Group 5 to 8; 477 children in total for the four schools). Because each school has different activities and interventions related to the Stadsscholen020 program we conducted a power calculation to estimate the sample size per school to ensure there is enough power to detect intervention effects over time. For this power calculation we used the general health-related quality of life in children (KIDSCREEN-10 index) as an indicator of our primary outcome Child Health. Using norm data [26] and pilot data from our sample we calculated that an effect size of 0.70 is related to a relevant change. Based on Cohen’s *d* this effect size is viewed as a large effect [34]. A sample size of 56 children per school was required to detect this effect size with 95% power when using a repeated measures ANOVA (within-between interaction) and a significance level (α) of 0.05. In correspondence with the stakeholders involved in this research project we accounted for an expected 30% dropout rate including both study dropout and natural dropout due to school change or migration. Therefore, the sample size per school is estimated at 73 children per school. Based on this power calculation we assume that the initially targeted population at baseline (*N* = 477) at the four schools is sufficient to detect a relevant change on the primary outcome measure.

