#### Data analysis

To investigate whether the Stadsscholen020 program leads to significant changes on primary and secondary outcomes over time, repeated measures ANOVAs and linear mixed models analysis techniques will be performed for this the longitudinal data. The linear mixed models technique is able the handle missing data using a likelihood based approach, every observation for every participant is used, irrespective of their missing data. The appropriate covariance structure, which accounts for the within-subject correlation, will be chosen based on the model fit using the − 2 log likelihood value. Cross-sectional data will be analysed by comparing means between the different levels (school, neighbourhood, district, and city level) using independent *t*-tests and ANOVA.

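### The sufficiency claim for 477 children compares a per-school longitudinal target with the T1 headcount and leaves out scheduled graduation; at T5 the smallest school misses 56 and the others have little or no margin

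*Protocol article*

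**What the plan says.** All places are in the protocol article.

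- *Power calculation for the primary outcome.* At the start, "the four schools have respectively 82, 119, 121, and 155 children in the targeted groups". Because activities differ between schools, "we conducted a power calculation to estimate the sample size per school". On the effect: "we calculated that an effect size of 0.70 is related to a relevant change". On the size: "A sample size of 56 children per school was required to detect this effect size with 95% power", for a within-between interaction in a repeated measures ANOVA at α = 0.05. The 30% allowance covers study dropout and "natural dropout due to school change or migration", and gives 73 per school. The section ends by assuming that the 477 children "at the four schools is sufficient to detect a relevant change on the primary outcome measure".
- *Participants and recruitment.* Five assessments are planned. "Therefore, the population will consist of a dynamic cohort throughout the school years", as laid out in Table 1. Children move on to secondary school at 11 or 12.
- *Data analysis.* "repeated measures ANOVAs and linear mixed models analysis techniques will be performed for this the longitudinal data". The mixed model is said to use every available observation.

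**The concern.** The requirement of 56 per school is for change within children over time, but it is checked against the number on the roll at T1. Table 1 shows that two of the four grades present at T1 finish primary school before T5. This loss is fixed by the calendar, and the power section does not mention it. The children who replace them (cohorts B and A) keep the roll full but have no T1 measurement, so they add nothing to a T1-to-T5 change.

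At stake is how per-school results are read. The protocol itself argues for calculating power by school, since each school runs different activities. If a school shows no change, a reader who trusts the stated 95% will take that as good evidence against a change of 0.70. In the smallest school at least, that reading would not be warranted.

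**Working it through.** **Inputs.** School sizes 82, 119, 121 and 155 (sum 477), 56 per school, d = 0.70, 95% power, α = 0.05 and 30% dropout come from the power section. Cohort schedule: Table 1. Assumption: equal grade sizes within each school, because the article gives school totals only.

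**1. The plan's own figures.**
- 56: a two-group comparison of means gives n = 2(1.960 + 1.645)²/0.70² = 53.04, so 54 per group; the exact t-test gives 55. Both are within two of 56. The named interaction test cannot be reproduced uniquely, because the numbers of groups and measurements and the correlation are not stated.
- 73: 56 × 1.30 = 72.8, rounded up. Dividing by retention gives 56/0.70 = 80. Every school exceeds 80 at T1, so this difference alone changes nothing.

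**2. Who can be measured (Table 1).** Of the T1 cohorts C, D, E and F:
- T1 and T2: all four, 100% of the T1 roll.
- T1 and T4: C, D and E, 75%.
- T1 and T5: C and D, 50%.

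**3. Expected children per school** = T1 roll × share still enrolled × retention.

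| Setting | 82 | 119 | 121 | 155 | Schools with at least 56 |
|---|---|---|---|---|---|
| Graduation ignored, 30% dropout | 57.4 | 83.3 | 84.7 | 108.5 | 4 |
| T1 and T4, 30% on top | 43.1 | 62.5 | 63.5 | 81.4 | 3 |
| T1 and T5, no dropout | 41.0 | 59.5 | 60.5 | 77.5 | 3 |
| T1 and T5, 30% on top | 28.7 | 41.7 | 42.4 | 54.3 | 0 (largest short by 1.75) |

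Among these settings, all four schools keep 56 only in the first row.

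**4. Sensitivity at T5.**
- Highest other dropout that still leaves 56, = 1 − 56/(half the roll): not attainable in the smallest school (41 < 56), then 5.9%, 7.4% and 27.7%.
- Share of the T1 roll that would have to be in Groups 5 and 6 to keep 56 after 30% dropout, = 80/roll: 97.6%, 67.2%, 66.1% and 51.6%.
- With no dropout at all, the smallest school would need 56/82 = 68.3% of its children in those two grades.

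**5. Illustrative power.** Scaling from the plan's anchor (56 children, d = 0.70, 95%) with one degree of freedom: power = Φ(3.605 × √(n/56) − 1.96), and d detectable at 95% power = 0.70 × √(56/n).

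| T1 and T5, 30% on top | n = 28.7 | 41.65 | 42.35 | 54.25 |
|---|---|---|---|---|
| Φ argument | 0.621 | 1.149 | 1.175 | 1.588 |
| Power | 73% | 87% | 88% | 94% |
| Detectable d | 0.98 | 0.81 | 0.80 | 0.71 |

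For the smallest school with no dropout (n = 41), power is about 87%. At T4 with 30% on top (n = 43.05), it is Φ(1.201), about 89%.

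**The case against.** A reader might infer that no school keeps the required 56. The documents do not support that as a fact, for three reasons.

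- *Grade sizes.* None are given. The largest school misses by under two children on an equal split and reaches 56 if 51.6% of its children are in Groups 5 and 6. This rescues the largest school only; the others would need implausibly uneven grades.
- *Double counting.* School change may be meant to include the move to secondary school, so adding the full 30% to graduation could count some children twice. That stands in part. At T4 graduation removes about 25%, so a 30% total could contain it, and the smallest school would then keep 57.4. At T5 graduation alone removes about 50%, which 30% cannot contain: the smallest school is at 41 with no other loss, and the middle two fall below 56 once other dropout passes about 6 to 7%.
- *The T1-and-T5 criterion.* The protocol does not say that the 56 must have T1 and T5 data, or that one ANOVA takes in all five waves. The intervention ends in July 2018, so T4 is the last assessment within it, and there three of four schools meet 56 even with 30% on top.

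The mixed model, which uses incomplete series and later entrants, is already planned, and Table 1 openly shows a changing cohort. This softens the consequence, but the 95% was calculated for the repeated measures ANOVA, and the article gives no power for the mixed model.

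The per-school power values are only a scaling. If school is the between factor, the named test is one interaction over all schools with several degrees of freedom, and it defines no separate power per school. Nor can one infer that the study as a whole is underpowered: pooled power is not given and cannot be derived from what is stated.

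**Conclusion.** The sufficiency statement is wrong as written, because it takes the T1 headcount as the number available for a longitudinal comparison and omits a loss that Table 1 schedules. Under equal grade sizes, the smallest school cannot supply 56 children with T1 and T5 data under any dropout rate (41 at most). The two middle schools can do so only if other dropout stays under about 6 to 7%. The largest is marginal if the full 30% is added. At T4 only the smallest school falls short, and only if most of the 30% is additional to graduation (above 1 − 56/61.5 = 8.9%).

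The likely cost in power is moderate in three schools (about 87% to 94% at T5 with 30% on top) and material in the smallest (about 73%). These values are illustrative. The conclusion rests on the equal-grade assumption, on T5 being part of the comparison, and on the plan's own 56 taken as given.

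**What to change.** - Withdraw the claim of 95% power in each school from the baseline 477.
- Replace it with a table of expected children per school at each wave after graduation and dropout, using the actual grade sizes and showing both T4 and T5.
- State whether graduation lies inside the 30%, and which waves the required 56 must contribute.
- Give the resulting power or detectable change per school and pooled, with the number of groups, the number of measurements and the correlation used.
- Make the already planned linear mixed model on all observations the primary longitudinal analysis; keep any complete-case repeated measures ANOVA as supportive only.

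The cost is some rewording, a short recalculation and less favourable per-school figures. No extra children are needed.

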#### Data analysis

To investigate whether the Stadsscholen020 program leads to significant changes on primary and secondary outcomes over time, repeated measures ANOVAs and linear mixed models analysis techniques will be performed for this the longitudinal data. The linear mixed models technique is able the handle missing data using a likelihood based approach, every observation for every participant is used, irrespective of their missing data. The appropriate covariance structure, which accounts for the within-subject correlation, will be chosen based on the model fit using the − 2 log likelihood value. Cross-sectional data will be analysed by comparing means between the different levels (school, neighbourhood, district, and city level) using independent *t*-tests and ANOVA.

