## Background

Children growing up in neighborhoods with high levels of poverty are at risk for negative developmental outcomes and inequality of their chances in life e.g., [1, 2]. Although children in the Netherlands have on average the lowest risk (11.9%) on poverty in the European Union, the number of children at risk of poverty on the three largest Dutch cities is still relatively high [3]. In Amsterdam, 1 on 4 children is at risk for growing up in poverty. On neighborhood level this number is even higher with regard to deprived neighborhoods in Amsterdam. Therefore, a substantial number of children in the Amsterdam neighborhood Holendrecht grow up in poverty. In this neighborhood already 27% of the households have an income up to 120% of the social minimum [4].

During the past decades, a large body of research has indicated the negative effects of childhood poverty on child health, well-being, and other developmental outcomes such as academic achievement. Yoshikawa, Aber, and Beardslee [5] outlined a conceptual framework emphasizing how poverty can deeply impact the emotional and behavioral health of children through a variety of mediating mechanisms. For example, children who grow up in low-income families are four times more likely to be in fair or poor health. Also, child obesity is more prevalent among children from low-income families compared to their more affluent peers [6]. With regard to mental health, children growing up in low-income households tend to express more emotional and conduct problems which is linked to impaired family functioning as a consequence of economic stress [7]. Recently, it was even shown that childhood poverty impacts the child’s brain development [8]. Another important factor rising the inequality of children’s chances in life is that the schools in disadvantaged neighborhoods tend to suffer from a variety of factors negatively affecting their quality and leading to lower academic achievement [9, 10]. For instance, schools with a large proportion of students from low-income families have more often less-effective teachers and a greater number of in-class disruptions than schools with a lower number of low-income students [10, 11].

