## Methods

### Design and study setting

The current study is an observational study within four primary schools located in Holendrecht, Amsterdam. Holendrecht is a neighborhood in the south eastern part of Amsterdam. Since the intervention is innovative and is being developed during the intervention period, we have chosen for this mixed-methods observational design. Stadsscholen020 is a new and complex intervention approach that comprises multiple interacting components and therefore we aim to evaluate policy, practice, and the implementation directly from the start of the intervention. Based on the mixed-methods design, our current study can be divided into three slightly overlapping and complementary study parts. First, we will conduct a longitudinal study (Part I) to evaluate the effects on the individual level for children using five assessment points. Second, in a cross-sectional study (Part II) we will evaluate the effects on school and neighborhood level. Third, using a process evaluation (Part III) we will study the implementation of the intervention and interpret our findings of the other study parts. For each study part different methods and instruments are used with regards to the data collection.

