### Eligibility criteria

In the initial pilot year (2015–2016) only four primary schools in Amsterdam Holendrecht neighborhood were focus of Stadsscholen020. Currently, eight other schools from deprived neighborhoods in Amsterdam are involved. The so called ‘Stadsscholen’ are selected based on their increased risk for educational disadvantages due to challenges and difficulties on family and neighborhood level (based on unpublished data from the municipality). Although there are more schools involved in the Stadsscholen020 program, for this research study we have chosen to focus on the four schools in the neighborhood Holendrecht since the interdisciplinary approach initially started at these schools. Because interdisciplinary approaches are time-consuming to implement in a school setting and it takes time to observe the potential effects, we have chosen for the schools with the longest intervention period. Also, our decision to focus on the four schools is based on considerations to limit the complexity of our study and conduct an in-depth process evaluation within the time frame of our study.

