#### Part II. Cross-sectional study

Complementary to the individual data and detailed information from the longitudinal and process evaluation, the cross-sectional study will include data from public databases of the municipality of Amsterdam (Onderzoek, Informatie en Statistiek, OIS), the Public Health Service of Amsterdam (GGD), and The Education Executive Agency of the Dutch Ministry of Education, Culture, and Science (Dienst Uitvoering Onderwijs, DUO). These data will be used to observe the effects of Stadsscholen020 during the intervention period on determinants related to health, poverty, and academic achievement that are available on school and neighborhood level. Data from the schools and the neighborhood where the schools are located (Amsterdam Holendrecht) will be compared with data on a wider district and city level. Table 2 shows the overview of the indicators related to the primary and secondary outcomes that will be examined in this cross-sectional study.

**Table 2 Tab2:** Overview of primary and secondary outcomes, indicators, and measurements

	Informants	Study parts		
		Longitudinal study *5 assessments*	Cross-sectional study *5 year period*	Process evaluation *5 assessments*
*Child Health*				
Life satisfaction (Cantril Ladder)	Child	×	×	
Socioemotional Well-being (SDQ)	Child	×		
Quality of life (KIDSCREEN)	Child	×		
Sport club membership	Child	×		
Dietary behavior (daily warm meal and fruit intake questions)	Child	×		
% 5-years old / 10-years old children with overweight (including obesity)	GGD		×	
% 5-years old / 10-years old children having breakfast every day	GGD		×	
% 5-years old / 10-years old children eating greens every day	GGD		×	
% 5-years old / 10-years old children that is physical active	GGD		×	
% Households supported by child welfare organizations (OKT)	GGD		×	
*Child Poverty*				
Family Affluence (FAS)	Child	×		
Stadspas ownership (minimal income permit)	Child	×		
% Households depending on social security benefits	OIS		×	
% Households having an income up to 120% of the social minimum	OIS		×	
% Children having parents with a lower education	OIS		×	
*Child Academic Achievement*				
Secondary school qualifications	DUO		×	
School test results (CITO)	DUO		×	
*School Environment*				
Teacher self-efficacy (TSES)	Teacher			×
Classroom climate (Class climate scale)	Teacher			×
School and neighborhood safety (additional questions)	Child			×
Bullying (KIDSCREEN and additional questions)	Child			×

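### Part II is meant to show programme effects during the intervention, but its stated test compares mean levels between overlapping areas that are expected to differ from the outset

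*Protocol article*

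**What the plan says.** The section on Part II gives it an effect aim: "These data will be used to observe the effects of Stadsscholen020 during the intervention period on determinants related to health, poverty, and academic achievement". The means is that figures for the schools and for Holendrecht "will be compared with data on a wider district and city level".

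The Data analysis section gives one sentence to these data: "Cross-sectional data will be analysed by comparing means between the different levels (school, neighbourhood, district, and city level) using independent" t-tests and ANOVA. The same paragraph analyses the longitudinal data over time. It gives Part II no before/after or level-by-time term, although the column heading of Table 2 assigns Part II a period of five years.

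Three other places bear on how that test behaves:
- **Selection.** Under Eligibility criteria, the programme schools were "selected based on their increased risk for educational disadvantages due to challenges and difficulties on family and neighborhood level". The Background section says of the risk of child poverty, put at 1 in 4 for the city: "On neighborhood level this number is even higher with regard to deprived neighborhoods in Amsterdam".
- **Nesting.** Under Design and study setting: "The current study is an observational study within four primary schools located in Holendrecht, Amsterdam", and "Holendrecht is a neighborhood in the south eastern part of Amsterdam".
- **Other programme schools.** Under Eligibility criteria: "Currently, eight other schools from deprived neighborhoods in Amsterdam are involved".

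**The concern.** An effect during the intervention period is a difference in change. The stated test looks at a difference in level. When the areas of interest were picked for disadvantage, a difference in level is expected whether or not the programme works. A significant result then carries no information about the programme, and a real improvement can be absorbed by the initial gap.

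The levels are also not separate samples. The schools lie in Holendrecht, and Holendrecht lies in the wider district and city with which it is compared. An independent-samples test assumes that no unit sits in both groups.

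In Table 2, Part II is the only source for overweight, which belongs to the primary domain, and for both listed indicators of academic achievement (secondary school qualifications and CITO results). A misread level difference would therefore feed directly into conclusions on those outcomes.

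**Working it through.** The article gives no sample size, effect size or power for Part II, so there is no figure to reproduce. What follows illustrates how the stated test behaves. The significance level of 0.05 is stated only for the Part I power calculation and is assumed here.

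**1. Significant result with no programme effect.** The 27% (Holendrecht households with an income up to 120% of the social minimum, Background) and the 477 (children in Groups 5 to 8, Power calculation) are used only to set a realistic scale. One counts households and the other children, so this is not a planned test. The comparator percentage and its size (10 or 100 times 477) are assumptions, because the article gives no district or city figure on the same measure.

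Rejection rate = Φ((|p1 − p2| − 1.96·SE0)/SE1), with SE0 = √(p̄(1 − p̄)(1/n1 + 1/n2)) and SE1 = √(p1(1 − p1)/n1 + p2(1 − p2)/n2).

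For 27% against 25% with n2 = 4770: p̄ = 0.2518, SE0 = 0.0208, SE1 = 0.0213. Then (0.02 − 0.0409)/0.0213 = −0.98, which gives about 0.163.

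| Assumed comparator | Gap (points) | Rejection, 10 times larger | Rejection, 100 times larger |
|---|---|---|---|
| 25% | 2 | 16.3% | 17.5% |
| 22% | 5 | 69.4% | 73.2% |
| 20% | 7 | 93.4% | 95.2% |
| 17% | 10 | 99.9% | 99.9% |

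**2. Masking, and what a change contrast does.** This is a simulation of five yearly percentages per level (assumed SD 1.5 points, 20,000 runs). A positive gap means that the programme area is worse. Any improvement falls in the last two of the five years. The expected level difference is gap − improvement × 2/5. The change contrast is the last-two minus first-three mean in the programme area, less the same quantity in the comparator.

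| Gap | True improvement | Mean level difference | t-test rejects | Mean change contrast |
|---|---|---|---|---|
| 0 | 0 | 0.0 | 5.0% | 0.0 |
| 2 | 0 | +2.0 | 45.6% | 0.0 |
| 5 | 0 | +5.0 | 99.6% | 0.0 |
| 2 | 5 | 0.0 | 0.2% | −5.0 |
| 5 | 3 | +3.8 | 83.5% | −3.0 |
| 5 | 5 | +3.0 | 34.1% | −5.0 |

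With a 2-point gap, a 5-point improvement vanishes (2 − 5 × 2/5 = 0). With a 5-point gap it still reads as a 3-point disadvantage. The change contrast recovers the improvement in each case, because a constant gap cancels.

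**3. Overlap.** Let f be the share of the larger group that the smaller one makes up.
- The part-minus-whole difference equals (1 − f) times the part-minus-rest difference.
- Its true variance is σ²(1/n − 1/N), while the independent test uses σ²(1/n + 1/N).
- The standard error is therefore too large by √((1 + f)/(1 − f)).

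Suppose the neighbourhood mean were formed by the four schools together (82 + 119 + 121 + 155 = 477):
- Smallest school: f = 82/477 = 0.172, difference shrunk to 83%, standard error 1.19 times too large, true two-sided level 0.020.
- Largest school: f = 155/477 = 0.325, difference shrunk to about 68%, standard error 1.40 times too large, true level 0.006.
- A small part of a city, f = 0.01 (assumed): ratio 1.01, true level 0.048.

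**The case against.** The best defence is that Part II is a supplement. The article calls it complementary to the individual data, change over time is analysed in Part I, and the power calculation rests on the KIDSCREEN-10 index. The Discussion concedes that causal relationships are hard to establish without randomised schools. An article condenses, and a fuller analysis plan could use the five years of data for a change comparison.

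Much of this is fair, and it limits the point to inference from Part II. It does not remove it. The article does more than leave the analysis open: it names a test, and that test does not answer the aim it states. The caveat in the Discussion is general and mentions neither the initial gap nor the overlap.

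Four stronger readings are tempting, and the documents do not support them:
- **That the nesting creates false-positive findings.** It works the other way, as step 3 shows. Only the initial gap produces spurious significance.
- **That the yearly figures measure the same population repeatedly.** Four of the public health service indicators concern 5- and 10-year-olds, and the school test and qualification data concern pupils at the end of primary school, so the children differ from year to year. Carry-over is plausible only for the household indicators. The article does not state the unit of analysis.
- **That the eight other programme schools seriously contaminate the city figure.** They are in Amsterdam, but no count of city schools is given, so the dilution could be trivial.
- **That academic achievement has no other source at all.** The School Environment section also uses teacher self-efficacy as an indicator of it, though an indirect one.

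**Conclusion.** The concern holds for inference about programme effects from Part II. Followed as written, the analysis tests whether a deprived area differs from its surroundings, which the selection of the schools already leads one to expect. The direction of the fault follows from the text alone.

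Its size depends on the gap, which the documents do not give. False significance ranges from about 16% to over 99% for assumed gaps of 2 to 10 points, so no single figure in that range should be quoted as the error rate. The masking results rest on the assumed yearly SD and timing of improvement.

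The overlap is a real but secondary breach of assumptions: conservative, material for school against neighbourhood, and negligible for a small part of a city.

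A reader might infer that the study's main evaluation fails. It does not follow, because Part I is analysed over time and is not touched by this point.

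**What to change.** Replace the sentence on cross-sectional data with a comparison of change over the planned five years, as a level-by-time interaction or difference-in-differences:
- Compare the schools and Holendrecht with comparators that do not contain them: the district without Holendrecht, and the city without the district.
- Leave the other eight programme schools out of school-level comparators where the data allow.
- Use standard errors that allow for area-by-year variation. With a single programme neighbourhood, treating yearly counts as plain binomial samples would make intervals too narrow.
- Date the five-year period and say which years count as before the programme, including how the 2015–2016 pilot year is classed.

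A change contrast removes a constant gap only. A gap that was already widening or narrowing would remain in the estimate, and this should be stated as an assumption.

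If there are too few pre-programme years, or denominators cannot be obtained, present the level comparison as descriptive and draw no conclusion about a programme effect from it.

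The cost is mainly a change of wording, since five years of data are already planned. It also needs a request for denominators and for figures on the remaining areas, and the article does not show whether these are available. The downside is wider intervals and a weaker claim for Part II.
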